| Inclusion Criteria | 
Both the patient and their guardian must meet the inclusion criteria to be eligible for participation in the study.
 
 
1. Patient 
 
① A patient diagnosed with advanced-stage solid cancer (ICD-10 code C00-C70) 
 
①-1. A patient undergoing or planning cancer treatment
 
 
 
② A patient who meets one of the following conditions: 
 
②-1. A patient with Eastern Cooperative Oncology Group (ECOG) performance status score of 2
 
②-2. A patient with an ECOG performance status score of 1 and aged 70 years or above
 
 
 
③ A patient who wishes to stay at home
 
④ A patient whose family guardian resides at home
 
⑤ A patient who wishes to participate in the study
 
 
 
2. Guardian 
 
① A family member of the patient
 
 
 
 
* Family: Patient's spouse (including de facto partners), lineal ascendant and descendant and their spouses, siblings and their spouses, and third cousins and their spouses.
 
 
② A patient who meets one of the following conditions: 
 
②-1. An individual living with the patient (a member of the patient's household)
 
②-2. An individual who does not live with the patient but visits the patient's home at least three times a week
 
 
 
③ An individual who wishes for the patient to live at home
 
④ An individual who can communicate with medical staff fluently
 
⑤ An individual who wishes to participate in the study
 
 |

|                     |                                                                                                                                                                                                                                                                                                                                                                                                                                                                                                                                                                                                                                                                                                                                                                                                                                                                                                                                                                                                                                                                                                                                                                                                                                                                                                                                                                                                                                                                                                                                                                                                                                                                                                                                                                                                                                                                                                                                                                                                                                                                                                                                                                                                                                                                                                                                                                                                                                         |
|---------------------|-----------------------------------------------------------------------------------------------------------------------------------------------------------------------------------------------------------------------------------------------------------------------------------------------------------------------------------------------------------------------------------------------------------------------------------------------------------------------------------------------------------------------------------------------------------------------------------------------------------------------------------------------------------------------------------------------------------------------------------------------------------------------------------------------------------------------------------------------------------------------------------------------------------------------------------------------------------------------------------------------------------------------------------------------------------------------------------------------------------------------------------------------------------------------------------------------------------------------------------------------------------------------------------------------------------------------------------------------------------------------------------------------------------------------------------------------------------------------------------------------------------------------------------------------------------------------------------------------------------------------------------------------------------------------------------------------------------------------------------------------------------------------------------------------------------------------------------------------------------------------------------------------------------------------------------------------------------------------------------------------------------------------------------------------------------------------------------------------------------------------------------------------------------------------------------------------------------------------------------------------------------------------------------------------------------------------------------------------------------------------------------------------------------------------------------------|
| Exclusion Criteria  | 
If the exclusion criteria apply to either the patient or their guardian, both are ineligible for participation.
 
1. Patient
 
 
① An individual who cannot speak, understand, or read Korean
 
② An individual who is judged by a physician to have a deplorable medical condition and is unable to participate in this study
 
③ An individual whose residence is located outside the range of home visits (the distance is specified in advance by each medical institution) for the medical staff of the respective medical institution (※)
 
④ An individual who has used inpatient or home hospice-palliative care services
 
※ Not applicable for the exclusion criteria of the control group
 
⑤ An individual under 19 years of age
 
 
2. Guardian
 
 
① An individual who cannot speak, understand, or read Korean
 
② An individual who is judged by a physician to have a deplorable medical condition and is unable to participate in this study
 
③ An individual under 19 years of age
 
                                                                                                                                                                                                                                                                                                                                                                                                                                                                                                                                                                                                                                                                                                                                                                                                                                                                                                                                                                                                                                                                                                                                                                                                                                                                      |
| Efficacy Assessment | 
1. Data Collection
 
1) Questionnaire
 
 
- Patients and guardians in both the intervention and control groups will complete a questionnaire at the time of participant registration.
 
- Participants in the intervention and control groups will complete a follow-up questionnaire 3 months after registration.
 
- Participants in the intervention group will complete an additional questionnaire 6 months after registration. In the case of the control group, only those who will provide consent to participate in the additional questionnaire at 3 months will complete the additional questionnaire at 6 months.
 
 
2) Medical Records Investigation
 
 
- Medical records at medical institutions will be investigated at 3, 6, and 12 months after the patient's registration for hospitalization (number and dates of hospitalizations), critical care use (date of ICU admission, date of ventilator support, and number of CPR attempts), and emergency room use (number of emergency room visits) at each time point.
 
- In the case of death at 3, 6, and 12 months after registration, the deceased patient's use of medical services (hospitalization, critical care use, and emergency room use) within one month of their death will be investigated.
 
 
3) Secondary Data Linkage
 
 
- For patients who will provide consent to secondary data linkages, the hospitalizations, medical expenses, death, type of end-of-life medical services used, and the use of emergency room, critical care, and hospice between the time of registration and 12 months will be investigated when all patients have been enrolled for 12 months or longer.
 
- Death, information related to hospice use, and the type of end-of-life medical services used will be investigated when all patients have been enrolled for 18 months or longer.
 
- For patients who will consent to secondary data linkages, whether legal forms for life-sustaining treatments (e.g., advance directives and physician orders for life-sustaining treatment) have been completed and by whom will be investigated at 12 and 18 months of enrollment when all patients have been enrolled for 12 and 18 months or longer, respectively.
 
 |

|                              |                                                                                                                                                                                                                                                                                                                                                                                                                                                                                                                                                                                                                                                                                                                                                                                                                                                                                                                                                                                                                                                                                                                                                                                                                                                                                                                                                                                                                                                                                                                                                                                                                                                                                                                                                                                                                                                                                                                                                                                                                                                                                                                                                                                                       |
|------------------------------|-------------------------------------------------------------------------------------------------------------------------------------------------------------------------------------------------------------------------------------------------------------------------------------------------------------------------------------------------------------------------------------------------------------------------------------------------------------------------------------------------------------------------------------------------------------------------------------------------------------------------------------------------------------------------------------------------------------------------------------------------------------------------------------------------------------------------------------------------------------------------------------------------------------------------------------------------------------------------------------------------------------------------------------------------------------------------------------------------------------------------------------------------------------------------------------------------------------------------------------------------------------------------------------------------------------------------------------------------------------------------------------------------------------------------------------------------------------------------------------------------------------------------------------------------------------------------------------------------------------------------------------------------------------------------------------------------------------------------------------------------------------------------------------------------------------------------------------------------------------------------------------------------------------------------------------------------------------------------------------------------------------------------------------------------------------------------------------------------------------------------------------------------------------------------------------------------------|
|                              | 
2. Efficacy Endpoints
 
 
- Primary endpoint: The number of unscheduled hospitalizations within 6 months of study enrollment.
 
* Unscheduled hospitalization: This includes hospitalization at a respective participating institution for acute treatments (excluding scheduled hospitalizations for anti-cancer treatments, operations, and procedures), hospitalization at medical institutions other than the participating institutions, or hospitalization of 4 weeks or less at a nursing hospital.
 
- Secondary endpoint
 
 
n Patient: Medical service use (e.g., hospitalization and ER visit), critical care use (e.g., ICU admission and ventilator support), use of end-of-life medical services (e.g., ICU admission one month before death and ventilator support), satisfaction with the services, quality of life (ESAS and EQ5D), affective disorders (PHQ9), and preparation of advance directives.
 
n Guardian: Satisfaction with the services, quality of life (EQ5D), burden of care (CRA-K), affective disorders (PHQ9), and care competency.
 
n Costs: Medical expenses and care costs
                                                                                                                                                                                                                                                                                                                                                                                                                                                                                                                                                                                                                                                                                                                                                                                                                                                                                                                                                                                                     |
| Safety Assessment            | Not applicable                                                                                                                                                                                                                                                                                                                                                                                                                                                                                                                                                                                                                                                                                                                                                                                                                                                                                                                                                                                                                                                                                                                                                                                                                                                                                                                                                                                                                                                                                                                                                                                                                                                                                                                                                                                                                                                                                                                                                                                                                                                                                                                                                                                        |
| Statistical Analysis         | 
The HBMC intervention group, control group, and each participating institution will be set as analysis groups for the statistical analysis of the outcome variables.
 
The analysis groups of the participants are based on the group assignment according to the initial intention-to-treat (ITT) that relies solely on the intervention of the original assignment to estimate the effectiveness in the intervention group conservatively. In the case of withdrawal of consent or dropout during follow-up, data collected till the time of withdrawal or dropout will be used. A comparative analysis of the dropout rate between the two groups will be performed and reported.
 
 
- Descriptive analysis of underlying characteristics
 
 
Continuous variables: mean (standard deviation) and median (IQR)
 
Dichotomous variables: frequency (%)
 
 
- Analysis of between-group differences
 
 
An analysis will be performed using a regression model while considering that participants, the observation units, were clustered into six participating institutions to evaluate the effects of the HBMC intervention and correcting for the differences in the baseline characteristics between the groups.
 
Dichotomous variable (primary endpoint): A generalized estimation equation (GEE) will be used to analyze the clusters of patients in participating institutions, and the effects of the HBMC intervention will be evaluated using a logistic regression model based on the logit link function.
 
Continuous variables: The effects of the HBMC intervention will be evaluated using a mixed model to consider the patient clusters in the participating institutions.
 
Count data: A GEE will be used to consider the patient clusters in the participating institutions, and the effects of the HBMC intervention will be evaluated using a regression model that appropriately uses Poisson and negative binomial as random components according to the distribution of variables using the logit link function as the link function.
 |
| Expected Effects and Results | Create a basis for the dissemination of the HBMC services for severely ill patients in Korea by developing a suitable HBMC model for severely ill patients in Korea and evaluating its effectiveness.                                                                                                                                                                                                                                                                                                                                                                                                                                                                                                                                                                                                                                                                                                                                                                                                                                                                                                                                                                                                                                                                                                                                                                                                                                                                                                                                                                                                                                                                                                                                                                                                                                                                                                                                                                                                                                                                                                                                                                                                 |

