### **A. Inclusion criteria**

#### ***1) Patients***

(1) A person who has an advanced-stage solid cancer diagnosis (ICD-10 Code C00-C70) and is receiving or planning to receive cancer treatment. (2) A person who meets one of the following conditions: (a) has been evaluated as having Eastern Cooperative Oncology Group (ECOG) performance status 2 or (b) has been evaluated as having ECOG performance status 1 and is aged above 65 years. (3) A person who wishes to stay at home (In South Korea, patients who need supportive care are usually hospitalized in long-term care hospitals due to the national insurance coverage and the lack of supportive care in cancer treatment hospitals. (4) A person who has a family caregiver *cohabiting with them or visiting their home three or more times per week*. (5) A person who wishes to participate in the research.

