### **B. Exclusion criteria**

#### ***1) Patients***

Patients will be excluded from the study if they (1) cannot speak, understand, or read Korean,

(2) are judged by a medical doctor to be unfit to participate in this research due to extremely poor health, (3) reside outside the geographical range that can be visited by the respective medical institution, (4) are already receiving hospice service, or (5) are aged below 19 years.

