## 12. Efficacy Endpoint Evaluation Criteria, Methods, and Interpretation

### A. Evaluation Criteria

#### *1) Primary Efficacy Endpoint*

- The proportion of patients with unscheduled hospitalization within 6 months of study enrollment
- Definition of an unscheduled hospitalization: hospitalization at a respective participating institution for acute treatments (excluding scheduled hospitalizations for anti-cancer treatments, operations, and procedures), hospitalization at other medical institutions other than the participating institutions, or **hospitalization of 4 weeks or less at a nursing hospital**

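### The protocol gives two versions of the home-visit distance exclusion and of the ECOG 1 age limit, and its primary endpoint filters out planned admissions only at the participating hospital, so the arms may not be comparable

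*Protocol*

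**What the plan says.** **Distance.** The Protocol Overview (Exclusion Criteria, patient item 3) excludes "An individual whose residence is located outside the range of home visits", with the distance set in advance by each institution. The item carries a reference mark whose note reads "Not applicable for the exclusion criteria of the control group". Section 5.B excludes patients who "reside outside the geographical range that can be visited by the respective medical institution" and makes no distinction between arms.

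**Age with ECOG 1.** The Overview admits "A patient with an ECOG performance status score of 1 and aged 70 years or above". Section 5.A admits a person who "has been evaluated as having ECOG performance status 1 and is aged above 65 years".

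**Primary endpoint.** Section 12.A, like the Overview, defines an unscheduled hospitalization by three routes:
- admission at the participating institution for acute treatment, "excluding scheduled hospitalizations for anti-cancer treatments, operations, and procedures";
- "hospitalization at other medical institutions other than the participating institutions";
- "hospitalization of 4 weeks or less at a nursing hospital".

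The removal of scheduled admissions stands in parentheses inside the first route only.

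**Capture of admissions.** Section 11.B has a research nurse review the records of the respective institution at 3, 6 and 12 months. For insurance-data linkage, the Overview (Efficacy Assessment) covers all consenting patients, while section 11.C speaks of consenting patients in the intervention group.

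**The concern.** Hospitals are not randomized and each belongs wholly to one arm, so common eligibility is a main protection of the comparison. Under the Overview, no intervention patient lives beyond home-visit range, but control patients may. Residence plausibly affects which hospital admits a patient, and outside hospitals are where the endpoint applies no filter for planned admissions and where capture is uncertain. A difference between arms in the primary endpoint could then arise from geography and record coverage, without any effect of home-based care.

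The age conflict is a separate point. ECOG 1 patients aged 66 to 69 are eligible under one text and ineligible under the other. By its wording this does not favour either arm. It would become an imbalance between arms only if hospitals followed different texts.

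**Working it through.** **1. The texts set against each other**

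| Distance rule in force | Linkage in both arms (Overview) | Linkage in intervention arm only (11.C) |
|---|---|---|
| Waived for controls (Overview) | Remote controls' outside admissions count, planned ones included: control rate can rise | Remote controls' outside admissions are missed: control rate can fall |
| Both arms (5.B) | No distance imbalance by design; planned outside admissions are still misclassified in both arms | No distance imbalance by design; capture still differs by arm |

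Three of the four combinations leave the arms treated differently on eligibility, on capture or on both. The protocol does not settle which one applies.

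**2. The plan's own power figure**

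Inputs from section 6: three clusters per arm, ICC 0.015, alpha 0.05, a 20-point difference, and 78.8% power at 57 per cluster. The two event rates are not stated; I assume 0.50 v 0.30 and a two-sided Wald test on the log odds ratio.

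- Effective n per arm = 3m / (1 + (m − 1) × ICC). For m = 57: 171 / 1.84 = 92.9.
- Log odds ratio = ln(0.50/0.50) − ln(0.30/0.70) = 0.847.
- SE = √[(1/0.25 + 1/0.21) / 92.9] = 0.307.
- Power = Φ(0.847/0.307 − 1.96) = 0.788, as printed.
- For m = 66: effective n = 198 / 1.975 = 100.3 and power = 0.818, against 0.830 printed, which is close.

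This only fixes a scale for what follows. It does not test the eligibility point.

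**3. Illustration, waiver in force, outside admissions captured in controls**

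Assumptions: control rate 0.50; a share r = 10–30% of controls live beyond range; a fraction q = 10–30% of those otherwise event-free gain an outside admission that counts. The endpoint is one yes/no per patient, so only event-free patients can add to it.

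- Rise = r × q × (1 − 0.50): 0.10 × 0.10 × 0.50 = 0.005, to 0.30 × 0.30 × 0.50 = 0.045.
- Chance of a significant result favouring the intervention with no true effect, effective n 100.3: 2.9% to 9.3%, against a nominal 2.5%. At the upper end, ln(0.545/0.455) = 0.1805, SE = 0.283, and Φ(0.638 − 1.96) = 0.093.

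**4. Illustration, waiver in force, outside admissions missed in controls**

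Assumptions: the same r; a fraction u = 25–75% of remote controls' events occur only outside and are not recorded.

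- Observed control rate = 0.50 × (1 − r × u): 0.50 × (1 − 0.025) = 0.4875, to 0.50 × (1 − 0.225) = 0.3875. The fall is 1.3 to 11.3 points.
- Power against an intervention rate of 0.30 drops from 0.82 to between 0.77 and 0.26.

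**The case against.** - **Direction.** A reader might infer that the waiver inflates the control rate and so favours home-based care. The document does not support that as a conclusion. It needs the Overview waiver to be operative and controls' outside admissions to be captured. Sections 11.B and 11.C read together suggest they may be missed, which pushes the other way. Section 11.C is itself not clear-cut, since a later sentence refers to patients in the intervention study, which could mean both groups.
- **Scope.** It is also tempting to say that every outside admission counts. That is too broad. Nursing-hospital stays count only up to 4 weeks, and an acute admission counts wherever it happens. The missing filter matters only for planned outside admissions. Patients are under cancer treatment, and ending treatment or follow-up at the hospital's oncology department is a suspension criterion (13.A). Nothing in the protocol shows planned outside admissions to be common.
- **Size.** Any figure for the bias as a share of the planned 20-point effect would rest on invented inputs. The protocol gives neither the share of remote controls nor their outside admission rate.
- **Adjustment.** The Overview already plans to correct for baseline differences, and the covariate list may sit in an analysis plan that is not shown. This stands in part. But under the waiver no intervention patient lives beyond the range, so a model would have to extrapolate to compare remote controls with anyone.
- **Age.** Nothing indicates that hospitals actually follow different texts. That stands, and it is why the age conflict is treated here as a contradiction to resolve, not as a bias.

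**Conclusion.** The point holds as a set of contradictions and one flaw in the endpoint definition. The distance exclusion differs between the Overview and section 5.B, the ECOG 1 age limit differs between the Overview and section 5.A, and planned admissions outside the participating institution count as unscheduled as written. These are stated rules, not details left for an analysis plan.

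The consequence is conditional. If the waiver is in force, the primary comparison can be biased. The control rate would be pushed upward if outside admissions are linked in both arms and downward if they are captured only in the intervention arm. The +0.5 to +4.5 and −1.3 to −11.3 point ranges are illustrations on an assumed 50% control rate and assumed shares, not estimates. Confidence is high on the text and low on direction and size. The protocol should be corrected on this, but nothing in it shows that the result will favour the intervention.

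**What to change.** 1. Reconcile the Overview exclusion and section 5.B to one distance rule for both arms. Control hospitals make no home visits, so the range that applies to them has to be written down.
2. Reconcile the Overview and section 5.A to a single age criterion for ECOG 1.
3. Reconcile the Overview and section 11.C on linkage, so that outside admissions are captured the same way in both arms.
4. Extend the scheduled-admission exclusion to other institutions. The linkage table in section 11.C lists admission route but no scheduled flag, so pre-state a proxy, such as admission through the emergency room, and apply it identically in both arms.
5. If remote controls are already enrolled, pre-specify an additional analysis limited to patients within a common distance in both arms, where the recorded residence (11.A) is detailed enough.

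**Cost.** Items 1 to 4 are mainly amendment wording; the proxy will misclassify some admissions, but equally by rule in both arms. Item 5 loses control patients. With 10–30% of controls removed at 66 per cluster and the assumptions above, power in that analysis falls from 0.82 to between 0.81 and 0.78. At 30%, control clusters average 66 × 0.7 = 46.2, effective n = 138.6 / (1 + 45.2 × 0.015) = 82.6, SE = √(4/82.6 + 4.762/100.3) = 0.310, and Φ(0.847/0.310 − 1.96) ≈ 0.78. At 57 per cluster the same calculation goes from 0.79 to between 0.78 and 0.75.
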